| RTS,S/AS02D                   | 25                    | Oil-in-water
emulsion | 25          | 25           | 0.5 mL         | Pediatric formulation
(Malaria-034, -038,
-040)                      |
| RTS,S/AS01B                   | 50                    | Liposomes                | 50          | 50           | 0.5 mL         | Efficacy in challenge
model (Malaria-027)                               |
| RTS,S/AS01E                   | 25                    | Liposomes                | 25          | 25           | 0.5 mL         | Proposed pediatric
formulation                                          |

The RTS,S/AS02A vaccine (0.25 mL dose) has demonstrated efficacy against infection and a range of illnesses caused by *P. falciparum* in children aged 1 to 4 years in Mozambique (Malaria-026). Up to 18 months post Dose 3 the VE determined as the time to the first clinical episode of malaria was 33%. VE against multiple attacks of malaria was 32% and against severe malaria was 49% over the 18 months of the trial.

The RTS,S/AS01 vaccines have been developed in parallel with the RTS,S/AS02 vaccines with the aim of improving the immune response and increasing vaccine efficacy. A recent challenge study with RTS,S/AS01B in malaria-naïve adults (Malaria-027) has shown encouraging results, indicating a similar safety profile to that of RTS,S/AS02A, higher humoral immunogenicity, a favorable Th1 cell-mediated immune profile and a trend towards higher vaccine efficacy.

RTS,S/AS01E (0.5 mL dose) is the proposed pediatric formulation which is composed of the same active constituents in the same quantities as a 0.25 mL dose of RTS,S/AS01B.

In light of those promising results, a study comparing the safety, immunogenicity and efficacy of RTS,S/AS02A with RTS,S/AS01B is underway in Kenyan adults (Malaria-044; BB-IND11220). Final study data reviewed by the Data Safety Monitoring Board from this trial will be available prior to starting Malaria-046. Age de-escalation will proceed with the proposed study which will be the first study to examine the administration of RTS,S/AS01E to children.

This trial is designed to evaluate safety, reactogenicity and immunogenicity of RTS,S antigen formulated in the adjuvant AS01E. The comparator group will receive RTS,S/AS02D.

This product development plan is conducted under a partnership agreement with the Malaria Vaccine Initiative at PATH (MVI) and is guided by a joint MVI/GSK Steering Committee.

This study is overseen by a formally constituted DSMB operating under a charter.

## **Objectives**

### **Coprimary**

- For RTS,S/AS01E when administered as 3 doses intramuscularly on a 0, 1, 2-month schedule to children aged 18 months to 4 years living in a malaria-endemic area:
  - to assess safety until one month post Dose 3

- to demonstrate non-inferiority to RTS,S/AS02D in terms of anti-CS antibody response one month post Dose 3.

**Secondary**

- For RTS,S/AS01E when administered as 3 doses intramuscularly on a 0, 1, 2-month schedule to children aged 18 months to 4 years living in a malaria-endemic area:
  - to assess reactogenicity until one month post Dose 3
  - to demonstrate non-inferiority to RTS,S/AS02D in terms of anti-HBs antibody response one month post Dose 3
  - to describe seroprotection against hepatitis B up to one month post Dose 3
  - to describe the anti-CS response up to one month post Dose 3.

**Tertiary**

- To assess, for RTS,S/AS01E when administered as 3 doses intramuscularly on a 0, 1, 2-month schedule to children aged 18 months to 4 years living in a malaria-endemic area:
  - safety between 1 month post Dose 3 until 12 months post Dose 3.
  - humoral immune response to CS antigen at 12 months post Dose 3
  - humoral immune response to HBs antigen at 12 months post Dose 3.

**Exploratory**

- For RTS,S/AS01E and RTS,S/AS02D when administered as 3 doses intramuscularly on a 0, 1, 2-month schedule to children aged 18 months to 4 years living in a malaria-endemic area:
  - to evaluate T-cell-mediated immune response (CMI) to CS antigen up to 12 months post Dose 3
  - to evaluate B-cell memory immune response to CS antigen up to 12 months post Dose 3
  - to describe the anti-CS response up to one month post Dose 3 according to documented HBV immunization status at screening

**Study design**

- Experimental design: Phase II, single center, double-blind (observer blind, participant blind), randomized (1:1 ratio) trial with two groups in one study site.

- Healthy male and female children aged 18 months to 4 years of age will be screened; those determined to be eligible, based on the inclusion and exclusion criteria, will be enrolled in the study.
- Route of administration: all vaccines will be administered by the intramuscular route to the left deltoid.
- Each child will be observed for at least 60 minutes after vaccination to evaluate and treat any acute adverse events (AEs).
- There will be a 7-day follow-up period for solicited AEs post-vaccination: Day 0 evaluation will be carried out by the study physician at the study center. Subsequently, trained field workers will visit the children to solicit AEs on days 1 to 6 after each vaccination (evaluation on Day 6 post Dose 1 will be carried out by the study physician at the study center).
- There will be a 30-day (day of vaccination and 29 subsequent days) follow-up after each vaccine dose for reporting unsolicited symptoms.
- Serious adverse events (SAEs) will be recorded throughout the study period. Prior to vaccination, any SAEs due directly to study procedures will be captured. All SAEs will be captured, beginning with the administration of the first dose and ending 14 months after Dose 1 of study vaccine. After the double-blind phase of the study, all enrolled children will be visited at home monthly by field workers until study conclusion to ensure complete identification of all SAEs.
- Safety review process: safety data from the first 40 children to receive Dose 1 and Dose 2 will be reviewed by the DSMB to authorize progression to the next sequential dose.
- This study will not capture cases of malaria for the analysis of efficacy. All cases of malaria presenting during the unsolicited period will be captured as unsolicited events. Cases at anytime during the study that meet the criteria for a SAE will be reported as SAEs.
- The access of the study population to HIV voluntary counseling and testing and HIV antiretroviral therapy according to national recommendations will be ensured, in collaboration with the government services.
- An insecticide impregnated bednet will be offered to all parent(s)/guardian(s) who present their child for screening.
- Blood for safety monitoring of hematology, renal and hepatic function will be measured at screening, one week post Dose 1, one month post Dose 3 and 12 months post Dose 3.

- Anti-CS antibody titers will be determined at screening, one month post Dose 2, one month post Dose 3 and 12 months post Dose 3.
- Anti-HBs antibody titers will be determined at screening, one month post Dose 2, one month post Dose 3 and 12 months post Dose 3.
- CMI and B-cell memory immune responses will be determined at screening, one month post Dose 2, one month post Dose 3 and 12 months post Dose 3.
- Timing of final analysis: 1 month post Dose 3. An annex safety analysis will be performed at the end of the study, one year post Dose 3.
- Data collection: conventional Case Report Form (CRF).

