### **5.1.3. Safety monitoring plan**

This trial is overseen by a Data Safety Monitoring Board (DSMB), operating under a charter, assisted by a Local Safety Monitor (LSM).

The DSMB will be notified of all SAEs within 24 hours. In addition there are defined points during the trial at which cumulative safety data will be reviewed by the LSM and the DSMB. There will be two reports as defined in Section 5.1.3.3.

The PI, LSM and DSMB are empowered to suspend the trial for any safety concern. To supplement this, the protocol defines criteria for the suspension of vaccination (refer to Section 5.1.3.4).

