**5.1.3.1.1. Data Reviewed by the DSMB**

The DSMB must be informed by the Local Safety Monitor (LSM) of the following safety data on an 'as received' basis:

- All SAEs;
- All withdrawals of study subjects by the Principal Investigator or the parent(s)/guardian(s) of a subject due to adverse events.

The DSMB will receive from the sponsor, GSK Biologicals:

- Safety summary reports at two predefined timepoints as defined in Section 5.1.3.3;
- New information that may affect adversely the safety of the subjects or the conduct of the study;
- All subsequent protocol amendments, ICF changes or revisions of other documents originally submitted for review;
- All subsequent protocol modifications (for information).

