**5.1.3.2. Local Safety Monitor (LSM)**

The overall role of the Local Safety Monitor (LSM), who is an experienced clinician based in Lambaréné, will be to support the clinical investigators and to act as a link between the investigators and the DSMB.

The LSM's role will include:

- Acting as the study volunteer's advocate;
- Promptly communicating relevant safety information to the DSMB;
- Providing advice to the investigators on whether a set of clinical circumstances in a study warrants formal notification to the DSMB;
- Unblinding a subject if deemed necessary to allow for adequate treatment;
- Liaising closely with the chair of the DSMB throughout the course of the trial;
- Suspension of vaccination for a major safety concern pending discussion with the DSMB (see Section 5.1.3.4 for full details).

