#### **5.1.3.3. Safety monitoring reports**

Safety reports will be produced for the DSMB on all data collected until two points in the study; after 40 subjects have been enrolled and have completed the first 7 days of follow-up post Dose 1 and after 40 subjects have completed the first 7 days of follow-up post Dose 2. An independent statistician will analyze the data and prepare an unblinded report for the DSMB thereby maintaining the blind of the malaria project team at GSK Biologicals and the investigator group. If a criterion for the suspension of progression to the next sequential vaccine dose is met, or the DSMB have any safety concerns about the vaccines, they may suspend the progression to the next vaccine dose. The process outlined in Section 5.1.3.4 will be followed.

The reports will contain for the first 40 children to receive each sequential vaccine dose:

- All SAEs and any relationship to vaccine (RTS,S/AS02D or RTS,S/AS01E) to date;
- For each of the first two doses (i.e. after Dose 1 and Dose 2) of RTS,S/AS02D and RTS,S/AS01E, all solicited AEs tabulated by severity grading (any and Grade 3 alone – refer to Table 9) and relationship to vaccine;
  - Should the investigator judge a case of Grade 3 fever to be unrelated to vaccination, an alternative explanation for the cause of the fever will be provided
- For each of the first two doses (i.e. after Dose 1 and Dose 2) of RTS,S/AS02D and RTS,S/AS01E, all unsolicited AEs tabulated by severity grading (any and Grade 3 alone – refer to Table 9) and relationship to vaccine;

- All laboratory values up to 30 days post Dose 2 presented as number of subjects out of range (above and below normal range) at each sampling time point (post doses 1 and 2 of RTS,S/AS02D or RTS,S/AS01E) tabulated by toxicity grading scale (refer to Table 10);
  - For all subjects with toxicity grading scale  $\geq 3$ , full clinical details will be provided
- All withdrawals of study subjects by the Principal Investigator due to adverse events recorded from the children or withdrawals of children by the parent(s)/guardian(s) following doses of RTS,S/AS02D or RTS,S/AS01E (expressed as percentage of subjects enrolled).

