#### **5.1.3.4. Process for the suspension of progression to the next sequential vaccine dose**

Suspension of the next sequential vaccine dose, pending full review of available data by the DSMB will take place if:

- The Principal Investigator suspends vaccination for any of the following SAEs pending review by the DSMB;
  - Death or life-threatening SAE which is judged to be related to the study vaccine;
  - Anaphylactic shock reaction in an enrolled subject following vaccination.
- The DSMB recommend suspension of all vaccination for any one SAE or pattern of SAEs. The DSMB will communicate their recommendation to the Principal Investigator who will enact it. The DSMB will notify the sponsors of their decision immediately;
- A safety report shows  $> 5\%$  of subjects vaccinated with RTS,S/AS01E, or  $> 5\%$  of subjects vaccinated with RTS,S/AS02D are withdrawn by the investigator for local or systemic reactogenicity in recipients;
  - In making their recommendation the DSMB will take into account the full clinical history of each withdrawn child.
- A safety report shows  $> 5\%$  of doses of RTS,S/AS02D or  $> 5\%$  of doses of RTS,S/AS01E are followed by fever  $> 39.0^{\circ}\text{C}$  judged to be related to vaccination in recipients of RTS,S/AS01E;
  - In making their recommendation the DSMB will review the investigators assessment of relatedness of all Grade 3 fevers (refer to Table 9).
- The DSMB recommend suspension of enrollment following their review of a safety summary reports.

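### The synopsis makes DSMB authorization a step before Doses 2 and 3, but the operating sections provide only for suspension, so early children could be re-dosed before the by-group review

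*Protocol*

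**What the plan says.** The Protocol synopsis (Study design, safety review process) sets a review of 40 children at each of the first two doses. It states that their safety data "will be reviewed by the DSMB to authorize progression to the next sequential dose". The synopsis rationale describes this trial as the one "which will be the first study to examine the administration of RTS,S/AS01E to children".

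The body describes the step differently:

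- **Section 5.1.3.3** triggers the first report "after 40 subjects have been enrolled and have completed the first 7 days of follow-up post Dose 1", and the second at the same point after Dose 2. An independent statistician prepares it unblinded. If a criterion is met or the DSMB is concerned, "they may suspend the progression to the next vaccine dose".
- **Section 5.1.3.4** begins "Suspension of the next sequential vaccine dose, pending full review of available data by the DSMB will take place if" and lists conditions. A report not yet reviewed is not among them.
- **Section 5.1.3.5** describes a decision to proceed to the next dose only for a trial already suspended.
- **Section 5.4** requires elimination criteria and contraindications to be checked before later doses. **Clinic Visits 4 and 5** (Section 5.11) add the identification card, adverse events and temperature. None mentions a DSMB decision.
- **Table 4** allows 21 to 35 days between doses, and Section 5.10 makes these intervals decide evaluability for the according-to-protocol (ATP) analyses.

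The text of Section 3 repeats much of the synopsis design list but not the safety review item. The figure there is not shown.

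**The concern.** The two rules give opposite instructions while a report is pending. Under an authorization rule, silence from the DSMB means wait. Under a suspension rule, silence means proceed. Staff who follow Section 5.4 and the visit lists would give Dose 2 on schedule without being told to look for a DSMB decision.

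At stake is the timing of the unblinded, by-group look at reactogenicity in the first paediatric use of RTS,S/AS01E. Two suspension rules in Section 5.1.3.4 depend on a safety report: more than 5% of subjects on either vaccine withdrawn for reactogenicity, and more than 5% of doses followed by related fever above 39.0°C. Neither can act before the report exists, so neither protects a child who has already had the next dose.

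**Working it through.** **Inputs from the Protocol.** Report 1 needs 40 children with 7 days of follow-up, which the endpoint definition counts as the day of vaccination plus 6 (Sections 5.1.3.3 and 10.2.1). Dose 2 is at Day 30, with a window of 21 to 35 days (Section 5.11, Table 4).

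**Inputs not stated.** D is the number of days from the first to the 40th Dose 1. T is the number of days from the 40th child's Day 6 to the DSMB decision. Both are assumed below.

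**Condition.** The decision falls on day A = D + 6 + T, counted from the first Dose 1. It precedes the first child's Dose 2 only if:

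- Day 30 dose: D + 6 + T ≤ 30, so D + T ≤ 24
- Day 35 dose: D + 6 + T ≤ 35, so D + T ≤ 29

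The same bounds apply to Dose 3 under the current text if doses fall on Days 0, 30 and 60. The second decision is on day D + 30 + 6 + T, and D + 36 + T ≤ 60 gives D + T ≤ 24. A third dose 35 days after the second (Day 65) gives 29.

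**Steady enrolment of r children per week.** Child i (i = 0 to 39) is dosed on day 7i/r, so D = 39 × 7/r = 273/r. The minimum rate is 273/(24 − T) for Day 30 and 273/(29 − T) for Day 35:

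- T = 7: 273/17 = 16.1 per week for Day 30; 273/22 = 12.4 for Day 35
- T = 14: 273/10 = 27.3 for Day 30; 273/15 = 18.2 for Day 35

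The number of children past Day 30 at the decision is the count of i with 7i/r + 30 < A, and likewise for Day 35. Each cell gives T = 7 / T = 14:

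| r per week | D | Decision day A | Past Day 30 | Past Day 35 |
|---|---|---|---|---|
| 5 | 54.6 | 67.6 / 74.6 | 27 / 32 | 24 / 29 |
| 10 | 27.3 | 40.3 / 47.3 | 15 / 25 | 8 / 18 |
| 15 | 18.2 | 31.2 / 38.2 | 3 / 18 | 0 / 7 |
| 20 | 13.65 | 26.65 / 33.65 | 0 / 11 | 0 / 0 |
| 30 | 9.1 | 22.1 / 29.1 | 0 / 0 | 0 / 0 |

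**Clustered vaccination.** If the first 40 are dosed within 10 days, D + T is at most 24 for any T up to 14, and no child passes Day 30 before the decision.

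**Effect of a hold at Dose 2.** Suppose early children are held to day A and the others are dosed on their own Day 30. The 40th Dose 2 is then on day D + 30 (for T up to 24), and the second decision is on day D + 36 + T. The first child's Dose 3 target is A + 30 = D + 36 + T, the same day. With the same T and no drop-out, no second hold arises.

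**The case against.** **The texts may be compatible.** The synopsis can be read as giving the purpose of the review, and Sections 5.1.3.3 to 5.1.3.5 as the process when the answer is no. Section 5.1.3.1 also commits the DSMB to confer at the points of safety review. A visit checklist need not carry a trial-level hold, since it does not list a check for suspension either. The charter and the Section 3 figure might supply the go-ahead. This stands in part: the intention is clear and the remedy may exist elsewhere. But a suspension has a stated trigger and a person to enact it. A pending report has neither, so the pre-dose instructions still lead to dosing.

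**Oversight continues without the report.** Section 5.1.3.1.1 reads "The DSMB must be informed by the Local Safety Monitor (LSM) of the following safety data on an" as-received basis, covering SAEs and withdrawals for adverse events. The Local Safety Monitor's role includes "Suspension of vaccination for a major safety concern pending discussion with the DSMB", and Section 5.1.3 adds: "The PI, LSM and DSMB are empowered to suspend the trial for any safety concern". Under Section 5.5, a Grade 3 general symptom found at a home visit brings the child to a clinician. All of this stands. What can come too late is the by-group tabulation and the two 5% rules.

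**Two stronger readings are not supported.** A reader might infer that slow enrolment forces the site to breach the synopsis, leave the Table 4 window or stop vaccinating. It does not. Screening may precede Dose 1 by up to 28 days (Table 4), and Appendix C has the site list interested families beforehand, so 40 screened children can be vaccinated close together even if recruitment is slow.

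A reader might also infer that the 7-day limit in Section 5.4 ends vaccination for a child waiting only for the DSMB. That paragraph is written around the illness and fever deferrals of Section 4.9.1, and Section 5.1.3.5 foresees proceeding to the next dose after a suspension. The limit deserves a clarifying sentence and no more.

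**Conclusion.** The inconsistency is real and should be fixed. The synopsis promises authorization before repeat dosing, and the operating sections would let dosing continue while the review is pending. Early repeat dosing is possible, not certain. It requires D + T above 24 days for a Day 30 dose, or above 29 for Day 35.

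Under evenly spread enrolment with a turnaround of 7 to 14 days, the number of children reaching Day 30 first runs from 0 at 30 per week to 15 or 25 at 10 per week. All these counts rest on assumed enrolment and turnaround, and clustered vaccination brings them to zero. Confidence is medium because the charter and the design figure are unseen.

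The effect on the immunogenicity analysis is limited. The plan allows for 180 − 150 = 30 non-evaluable children, and Section 10.8.2 adds a Total Vaccinated Cohort analysis if ATP exclusions exceed 5%.

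**What to change.** 1. State in Sections 5.1.3.3 and 5.1.3.4 that no child receives Dose 2 or Dose 3 until the DSMB decision on the corresponding report is on file.
2. Add that check to Section 5.4 and to Clinic Visits 4 and 5.
3. Schedule the first 40 Dose 1 vaccinations and the report so that D + T is at most 29 days, which puts the decision within the first child's 35-day window.
4. As a clarification only, state that the 7-day limit in Section 5.4 applies to Section 4.9.1 deferrals and not to a DSMB hold.

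The cost is protocol wording, one line in the pre-dose checks and tighter scheduling, with no extra children. The downside is a possible one-time delay of Dose 2 for the earliest children. At 10 per week without clustering, the first child would wait until about Day 40 (T = 7) or Day 47 (T = 14), and 8 or 18 children would receive Dose 2 outside the Table 4 window.

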**Number of subjects**

180 subjects will be enrolled. It is expected that approximately 150 subjects will be evaluable at study end.

**Primary endpoints****Safety**

- Occurrence of SAEs from the time of first vaccination (Study Month 0) until one month post Dose 3 (Study Month 3).

**Immunogenicity**

- Anti-CS antibody titers one month post Dose 3.

**Secondary endpoints****Safety and Reactogenicity**

- Occurrence of solicited general and local reactions over a 7-day follow-up period (day of vaccination and 6 subsequent days) after each vaccination.
- Occurrence of unsolicited symptoms after each vaccination over a 30-day follow-up period (day of vaccination and 29 subsequent days).

**Immunogenicity**

- Anti-CS antibody titers prior to vaccination, one month post Dose 2 and one month post Dose 3.
- Anti-HBs antibody titers prior to vaccination, one month post Dose 2 and one month post Dose 3.

**Tertiary  
endpoints****Immunogenicity***At Study Month 14:*

- Anti-HBs antibody titers determined 12 months post Dose 3.
- Anti-CS antibody titers determined at 12 months post Dose 3.

**Safety**

- Occurrence of SAEs from 1 month post Dose 3 until 12 months post Dose 3.

**Exploratory  
endpoints****Cell-Mediated Immunity**

- Frequency of CS-specific T-cells prior to vaccination, one month post Dose 2, one month post Dose 3 and 12 months post Dose 3.
- Frequency of CS-specific B-cell memory prior to vaccination, one month post Dose 2, one month post Dose 3 and 12 months post Dose 3.
- Anti-CS antibody titers determined at 12 months post Dose 3 according to documented HBV immunization status at screening

## List of Abbreviations

|            |                                                                          |
|------------|--------------------------------------------------------------------------|
| AE         | Adverse event                                                            |
| ALT        | Alanine aminotransferase                                                 |
| anti-CS    | Antibody to the P. falciparum circumsporozoite (CS) repeat domain |
| anti-HBsAg | Antibody to the hepatitis B surface antigen                              |
| ATP        | According to protocol                                                    |
| CI         | Confidence interval                                                      |
| CMI        | Cell-mediated immunity                                                   |
| CRA        | Clinical research associate                                              |
| CRF        | Case report form                                                         |
| CS         | Circumsporozoite protein of P. falciparum                         |
| CSC        | Central study coordinator                                                |
| DSMB       | Data safety monitoring board                                             |
| EIA        | Enzyme immunoassay                                                       |
| EIR        | Entomological inoculation rate                                           |
| EISR       | Expedited investigator safety report                                     |
| ELISA      | Enzyme linked immunoassay                                                |
| EPI        | Expanded program on immunization                                         |
| FDA        | Food and Drug Administration, United States                              |
| GCP        | Good clinical practice                                                   |
| GMT        | Geometric mean titer                                                     |
| GSK        | GlaxoSmithKline                                                          |
| HAS        | Albert Schweitzer Hospital (Hôpital Albert Schweitzer)                   |
| HBs        | Hepatitis B surface antibody                                             |
| HBsAg      | Hepatitis B surface antigen                                              |

|                      |                                                                                                                                 |
|----------------------|---------------------------------------------------------------------------------------------------------------------------------|
| HBV                  | Hepatitis B virus                                                                                                               |
| HIV                  | Human immunodeficiency virus                                                                                                    |
| IB                   | Investigator's brochure                                                                                                         |
| ICF                  | Informed consent form                                                                                                           |
| IEC                  | Independent ethics committee                                                                                                    |
| IFN- $\gamma$        | Interferon gamma                                                                                                                |
| IM                   | Intramuscular                                                                                                                   |
| IND                  | Investigational new drug                                                                                                        |
| IRB                  | Institutional review board                                                                                                      |
| IU                   | International unit                                                                                                              |
| ITN                  | Insecticide-treated bednet                                                                                                      |
| kg                   | Kilogram                                                                                                                        |
| LSM                  | Local safety monitor                                                                                                            |
| MedDRA               | Medical Dictionary for Regulatory Activities                                                                                    |
| mg                   | Milligram                                                                                                                       |
| mL                   | Milliliter                                                                                                                      |
| MPL ®     | 3-deacylated monophosphoryl lipid A                                                                                             |
| MRU                  | Medical Research Unit, Albert Schweitzer Hospital                                                                               |
| MVI                  | Malaria Vaccine Initiative                                                                                                      |
| P. falciparum | Plasmodium falciparum                                                                                                    |
| PATH                 | Program for Appropriate Technology in Health                                                                                    |
| PFS                  | Pre-filled syringe                                                                                                              |
| PPP                  | Pre-patent period                                                                                                               |
| QS 21                | ' Quillaja saponaria 21': a triterpene glycoside purified from the bark of the soap bark tree, Quillaja saponaria |
| RAP                  | Report and Analysis Plan                                                                                                        |

|       |                                                                              |
|-------|------------------------------------------------------------------------------|
| RTS   | Hybrid protein comprising HBs (hepatitis B surface antigen) and CSP portions |
| RTS,S | Particulate antigen, containing both RTS and HBs proteins                    |
| SAE   | Serious adverse event                                                        |
| SOP   | Standard operating procedure                                                 |
| SP    | sulfadoxine-pyrimethamine                                                    |
| ULN   | Upper Limit of Normal                                                        |
| VCT   | Voluntary Counseling and Testing                                             |
| VE    | Vaccine efficacy                                                             |
| WHO   | World Health Organization                                                    |
| WRAIR | Walter Reed Army Institute of Research                                       |

